#### Primary outcomes

2.5.1

1. **GSRS.**
a.**Timeframe**: Pre-FMT, during FMT, and at 1, 2, 3, 4, 5, 6 weeks, 3 months, 6 months,9 months and 12months post-FMT.b.**Description**: A 15-item questionnaire evaluating GI symptom severity. Each item is scored from 1 (“none”) to 7 (“very severe”), with descriptors: 1 (none), 2 (mild), 3 (slight), 4 (moderate), 5 (marked), 6 (severe), 7 (very severe). Participants with <50% reduction in mean GSRS scores are classified as non-responders.**2. CARS**
a.**Timeframe**: Pre-FMT, 3 months, 6 months,9 months and 12 months post-FMT.b.**Description**: Administered by trained assessors, this 15-item scale yields a total score ranging from 15 to 60. Scores are interpreted as: <30 (non-autistic), 30–36 (mild-to-moderate autism), and ≥36 (moderate-to-severe autism).

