**Methods:**

This open-label single-arm trial enrolls 30 children (2–12 years) with moderate-to-severe ASD, defined as a Childhood Autism Rating Scale (CARS) score of ≥36. Participants receive 3 nasojejunal FMTs (5 mL/kg) over 5 days. The primary outcomes are GI symptom improvement, assessed using the Gastrointestinal Symptom Rating Scale (GSRS), and ASD severity, assessed using the CARS. Secondary outcomes include social responsiveness (Social Responsiveness Scale, SRS), aberrant behaviors (Aberrant Behavior Checklist, ABC), and gut microbiota changes assessed by metagenomic next-generation sequencing (mNGS).

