
However, FMT's clinical application remains contentious:
**Inconsistent Efficacy:** A randomized controlled trial (RCT) found no significant difference between oral FMT capsules and placebo, potentially due to donor variability or administration routes (30).**Safety Concerns:** Although most adverse effects (AEs) are mild to moderate, risks such as infections and long-term safety in ASD patients require further evaluation (31, 32).**Unclear Mechanisms:** While FMT alters gut microbiota composition in ASD, the pathways linking microbial changes to symptom improvement (e.g., specific metabolites or immune pathways) remain undefined, hindering biomarker-guided personalized therapy (33).**Uncertain Long-term Outcomes:** Long-term follow-up studies report diminishing therapeutic effects over time, with partial relapse of core symptoms in some patients (31).The complexity of ASD demands interdisciplinary collaboration. As a powerful tool to modulate the MGBA, FMT holds promise for addressing neurodevelopmental deficits at their root. Despite current limitations, advancements in mechanistic understanding, technological innovation, and clinical standardization may position FMT as a cornerstone of precision medicine for ASD, offering new hope for affected children and families. Future efforts must balance scientific rigor with clinical translation to bridge the gap between laboratory research and real-world therapeutic applications. Therefore, we hypothesize that multi-course FMT will significantly improve both GI symptoms and core behavioral deficits in children with moderate-to-severe ASD, and that these clinical improvements will be associated with the restoration of gut microbial diversity and function.

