#### Analysis of clinical outcomes

2.7.1

Analysis of clinical data (CARS, GSRS, SRS, ABC) will be conducted using SPSS 26.0. Continuous variables will be expressed as mean ± standard deviation. For comparisons between baseline and specific follow-up points, paired *t*-tests or Wilcoxon signed-rank tests will be used, as appropriate based on data distribution. To analyze the longitudinal changes in primary and secondary outcomes over the multiple time points, linear mixed-effects models will be employed to account for intra-subject correlations.

To ensure the highest standard of statistical analysis, we have formally engaged a qualified statistician as a consultant for this study. The statistician will be involved in the final data analysis plan, execution, and interpretation of results.

The primary analysis of clinical outcomes will be conducted on the per-protocol (PP) population, defined as all participants who complete the primary endpoint assessment at 12 months. A secondary analysis will be performed on the intent-to-treat (ITT) population, which includes all enrolled participants who have received at least one Fecal Microbiota Transplantation administration. For longitudinal data (e.g., GSRS), linear mixed-effects models are inherently robust to data missing at random. For missing primary endpoint data (e.g., 12-month CARS), multiple imputation techniques will be explored and applied if necessary, under the guidance of our study statistician.

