### Sample size calculation

2.8

The sample size for this prospective single-arm study was determined based on the primary outcome of the change in the CARS score from baseline to 12 months post-intervention. The calculation is based on the 12-month follow-up data from a large-scale preliminary study by Ye et al. (2022) on FMT for children with ASD (31).

In that study, the mean CARS score in children with ASD before treatment was 35.2 ± 6.5. Following FMT, the mean score at 12 months post-treatment was 31.0 ± 6.7. This represents a mean reduction (δ) of 4.2 points, which is considered the clinically significant difference to be detected in this protocol.

The standard deviation of the difference (*σd*) is required for the calculation. Assuming a conservative correlation coefficient (*r*) of 0.5 between baseline and 6-month measurements (a common assumption for pre-post study designs), the standard deviation of the difference can be estimated using the formula:$$\sigma_{d}=\sqrt{\sigma_{\;pre}^{2}+\sigma_{\;post}^{2}-2r\sigma_{\;pre}\sigma_{\;post}}$$This yields an estimated *σd* of approximately 6.60.

Using a two-sided paired *t*-test, with a significance level (*α*) of 0.05 and a desired statistical power (1-*β*) of 80% $\left(Z_{\beta }=0.8416\right)$, the required sample size (*n*) was calculated using the following formula: $n=(Z_{\alpha /2}+Z_{\beta }{)}^{2}\sigma_{d}^{2}/\delta^{2}$.Therefore, *n* = [(1.96 + 0.8416)^2^ × 6.60^2^]/(4.2^2^) ≈ 19.4.

Based on these parameters, the minimum required sample size is calculated to be 20 participants.

To account for a potential dropout rate of approximately 20% during the 6-month follow-up period, the sample size needs to be adjusted.

Adjusted sample size = *n*/(1—dropout rate) = 20/(1–0.20) = 25.

Therefore, the planned enrollment of 30 participants is more than sufficientto provide adequate statistical power for evaluating the primary outcome of this study.

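### Two primary outcomes are named without a primary visit, but the stated alpha and power cover only the 12-month CARS change

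*Protocol article*

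**What the plan says.** The Methods paragraph of the abstract names two primary outcomes: "The primary outcomes are GI symptom improvement, assessed using the Gastrointestinal Symptom Rating Scale (GSRS), and ASD severity, assessed using the CARS". Section 2.5.1 (Primary outcomes) repeats both and gives each a timeframe:

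- GSRS: "Pre-FMT, during FMT, and at 1, 2, 3, 4, 5, 6 weeks, 3 months, 6 months,9 months and 12months post-FMT". That is 11 post-baseline assessments: one during treatment, six weekly, and months 3, 6, 9 and 12.
- CARS: "Pre-FMT, 3 months, 6 months,9 months and 12 months post-FMT". That is 4 post-baseline assessments.

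Neither entry marks a visit as primary.

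Section 2.7.1 (Analysis of clinical outcomes) says: "For comparisons between baseline and specific follow-up points, paired *t*-tests or Wilcoxon signed-rank tests will be used". It does not name those points. For the repeated measurements it adds that "linear mixed-effects models will be employed to account for intra-subject correlations", without singling out a contrast. The same section points to 12 months twice: once when it defines the per-protocol population, and once when it gives 12-month CARS as its example of missing primary endpoint data.

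Section 2.8 (Sample size calculation) uses the singular. The size was "based on the primary outcome of the change in the CARS score from baseline to 12 months post-intervention", with a two-sided paired t-test, alpha 0.05 and 80% power. GSRS does not enter the calculation.

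The Introduction hypothesises that treatment "will significantly improve both GI symptoms and core behavioral deficits in children with moderate-to-severe ASD".

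**The concern.** A reader of 2.5.1 would expect two primary results. A reader of 2.8 would expect one. Which is meant decides what the 5% and the 80% refer to. As written, a significant GSRS result could be reported as meeting a primary outcome although no alpha was set aside for it and no power was calculated. A null 12-month CARS result could then sit beside a trial described as positive on a primary outcome.

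The hypothesis speaks of both domains, but the text does not say whether success needs both scales, either one, or CARS alone. These three rules have different error rates and different power.

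**Working it through.** **1. The plan's own figure (section 2.8).** Inputs: SD 6.5 before and 6.7 after treatment, r = 0.5, difference 4.2, two-sided alpha 0.05, power 80%, dropout 20%.

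- σd = √(6.5² + 6.7² − 2 × 0.5 × 6.5 × 6.7) = √43.59 = 6.60
- n = (1.96 + 0.8416)² × 43.59 / 4.2² = 19.4, so 20
- 20 / (1 − 0.20) = 25, with 30 planned

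The figures reproduce. They are right for one test, the 12-month CARS change. With 30 × 0.8 = 24 completers, the exact (noncentral t) power of that test is about 85%.

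**2. Count of assessments (section 2.5.1, agreeing with Table 1).** GSRS 11 + CARS 4 = 15 post-baseline assessments.

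**3. Narrow reading: both scales tested at 12 months, each at 0.05, unadjusted.** If the scales are independent and nothing changes:

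- at least one p < 0.05: 1 − 0.95² = 9.75%
- at least one favourable p < 0.05: 1 − 0.975² = 4.9%, against 2.5% for one test

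Simulation with 24 children gives 9.4% to 9.9% for the first figure. It assumed a within-scale correlation between visits of 0.5 to 0.9 and a correlation parameter between scales of 0 to 0.3.

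**4. Wide reading: every visit on both scales tested against baseline, unadjusted.** Fifteen independent tests would give 1 − 0.95¹⁵ = 53.7%. The tests are not independent, because all visits on a scale share one baseline. Simulation allowing for this, under the same assumptions, gives:

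- any of the 15 tests: 41% to 42%
- any of the 11 GSRS tests: 30% to 32%
- any of the 4 CARS tests: about 16%
- any favourable result among the 15 (scales independent, r = 0.5 or 0.7): about 22%

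**5. If both scales had to succeed at one fixed visit each.** The chance of a false claim cannot exceed the 5% of either test, so there is no inflation. Power would then also depend on GSRS, for which 2.8 gives no calculation.

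**6. If alpha were split equally (0.025 each).** By the formula of 2.8, n = (2.2414 + 0.8416)² × 43.59 / 4.2² = 23.5, so 24, and 24 / 0.8 = 30. By exact t the requirement is 27, or 34 after dropout, and power for CARS with 24 completers is 76%. The planned 30 would just meet the plan's own formula and fall short by the exact calculation.

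**The case against.** The case on the other side has force on several points.

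- **The plan promises no familywise rate.** A reader might infer that a claimed 5% error rate for the whole trial is broken. The document does not support that: 0.05 is the level of one paired t-test, and for that test it holds. What stands is that the 0.05 does not extend to GSRS.
- **Assessment times are not tests.** It is tempting to read 2.5.1 as 15 unadjusted primary tests and to lead with 42%. Section 2.7.1 speaks only of "For comparisons between baseline and specific follow-up points", assigns the repeated data to mixed models, and points twice to 12 months. The narrow figure of about 10% is therefore the fairer one, and 42% is an upper reading.
- **The word both may mean that both scales must succeed.** Then nothing is inflated. No such rule is written, however, so this is one possible reading and does not resolve the question.
- **A multiplicity rule may be in the analysis plan.** That plan is not shown, and the lack of such a rule in the article is not the finding. The finding is that 2.5.1 has two primary outcomes where 2.8 has one. An analysis plan could choose between them but would leave the published sections in conflict.
- **The trial is exploratory.** The Discussion says so and concedes placebo effects, natural course and observer bias. Adjusting p-values would not make a single-arm pre-post change confirmatory. This lowers the severity. It does not reconcile the two sections, and the text still hypothesises significant improvement and makes a power claim.

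A reader might also infer that early GSRS scores are distorted by the bowel lavage or tube placement. The document describes those procedures but says nothing of their effect on GSRS, and this point does not rely on it.

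**Conclusion.** The contradiction holds: the abstract and 2.5.1 name two primary outcomes, while 2.8 sizes the trial on one. The stated alpha and power describe only the 12-month CARS change.

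Unadjusted testing of both scales at 12 months carries about a 10% chance of at least one false positive, or about 5% in the favourable direction, assuming independent scales. If every visit were tested, the figure would be about 42%. That assumes 24 completers, a within-scale correlation of 0.5 to 0.7 and independent scales, and it is an upper reading of an ambiguous text. The correlations are assumptions because the document gives none between visits beyond the 0.5 used in 2.8.

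The point should be fixed, but it does not undermine the sample size, which is correct for the test it names. The document shows an ambiguity over the primary test. It does not show that inflated testing is planned.

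**What to change.** In 2.5.1 and 2.7.1:

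- Name the change in CARS from baseline to 12 months as the single primary test at two-sided 0.05. This is the endpoint and alpha on which 2.8 is sized.
- Name the method. Section 2.8 uses a paired t-test. If the 12-month contrast from the mixed model is preferred, say so in 2.8 as well.
- Test the GSRS change at one fixed visit, such as 12 months, only if CARS is significant. This sequence keeps the error over the two tests at 5%. It is gatekeeping: CARS can succeed alone, and improvement in both domains may be claimed only if both steps succeed.
- Report all other visits as estimates with confidence intervals, without claims of significance.

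Bring the abstract into line. The cost is wording, made before outcome data are examined, and the planned 30 children stand. The downside is that GSRS loses its stand-alone primary claim. If the sponsor wants to keep that claim, splitting alpha or requiring both scales to succeed are valid alternatives. Either would need 2.8 to be redone, including a power calculation for GSRS.

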##### Pre-FMT preparation

2.4.4.1

Patients will begin a semi-liquid diet one day prior to the first FMT administration. Prior to the FMT procedure, all participants will undergo bowel preparation with polyethylene glycol (PEG) lavage to cleanse the intestinal tract, which is consistent with our clinical practice. Given that the FMT is delivered directly to the jejunum, the use of proton-pump inhibitors (PPIs) or other acid suppressants is not planned for this protocol.

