#### Secondary outcomes

2.5.2

1.Daily Stool Record (DSR)
a.**Timeframe**: Pre-FMT, during FMT, and at 1, 2, 3, 4, 5, 6 weeks, 3 months, 6 months, 9 months and 12 months post-FMT.b.**Description**: Daily documentation of stool characteristics using the Bristol Stool Scale. The percentage of days with abnormal bowel movements (e.g., abnormal consistency, absence of stool, or use of GI medications) is calculated, with higher percentages indicating worse symptoms.2.Social Responsiveness Scale (SRS)
a.**Timeframe**: Pre-FMT, 3 months, 6 months,9 months and 12 months post-FMT.b.**Description**: A 65-item questionnaire assessing social skills. Items are scored 0 (“never true”) to 3 (“almost always true”), with total scores ranging from 0 to 195. Higher scores indicate greater social impairment.3.Aberrant Behavior Checklist (ABC)
a.**Timeframe**: Pre-FMT, 3 months, 6 months,9 months and 12 months post-FMT.b.**Description**: A 58-item checklist evaluating maladaptive behaviors. Total scores range from 0 to 174, with ≥31 indicating autism tendency and >53 confirming an autism diagnosis. Higher scores reflect more severe behavioral issues.4.Microbiota Analysis
a.**Sequencing Method:** Fecal samples will be subjected to metagenomic next-generation sequencing (mNGS) to comprehensively characterize the gut microbiota at both taxonomic and functional levels. Total microbial DNA will be extracted from fecal samples, followed by library construction and shotgun sequencing on an Illumina NovaSeq platform (or equivalent), aiming for a sequencing depth of at least 10 Gbp per sample to ensure adequate coverage for both abundant and rare species, as well as functional gene analysis.b.Bioinformatic and Statistical Analysis Pipeline:

The raw sequencing data and subsequent analyses will adhere to the following rigorous bioinformatics procedure to ensure accuracy and reproducibility.

Step 1: Raw Data Quality Control.

To assess sequencing quality and detect potential contamination, FastQC (Version 0.12.1) (36) and MultiQC (Version 1.15) (37) will be utilized with default parameters. Key quality metrics include ≥80% of bases with a Q-score >30, adapter content <5%, and GC distribution within the expected range of 40%–50%. The output report, ASD_FMT_Raw_QC.html, will be reviewed to exclude samples that fail to meet these criteria.

Step 2: Read Trimming and Host DNA Removal.

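### Treatment-period GSRS and stool records are listed as outcome time points, and the abnormal-day rule does not exempt the protocol's own bowel lavage

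*Protocol article*

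**What the plan says.** Section 2.5.1 gives the GSRS timeframe as "Pre-FMT, during FMT, and at 1, 2, 3, 4, 5, 6 weeks", followed by months 3, 6, 9 and 12. It also sets a responder rule: "Participants with <50% reduction in mean GSRS scores are classified as non-responders". The rule names no visit.

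Section 2.5.2 gives the Daily Stool Record (DSR) the same schedule: "Pre-FMT, during FMT, and at 1, 2, 3, 4, 5, 6 weeks, 3 months, 6 months, 9 months and 12 months post-FMT". A day is abnormal for, among other things, "abnormal consistency, absence of stool, or use of GI medications) is calculated, with higher percentages indicating worse symptoms". Table 1 ticks GSRS and DSR in the treatment-period column.

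Section 2.4.4.1 requires that "all participants will undergo bowel preparation with polyethylene glycol (PEG) lavage to cleanse the intestinal tract" and starts a semi-liquid diet the day before the first infusion. It does not say on which day, or how often, lavage is given. Section 2.4.4.2 describes endoscopic nasojejunal tube placement under sedation and acknowledges that it is uncomfortable. Section 2.4.4.3 puts the infusions on Days 1, 3 and 5.

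For change over time in primary and secondary outcomes, Section 2.7.1 says that "linear mixed-effects models will be employed to account for intra-subject correlations". It does not exclude the treatment-period record. Section 2.6 also uses GSRS and DSR to follow GI status for safety, but no section restricts the treatment-period values to that use.

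**The concern.** A score taken while a child is being prepared, sedated, intubated and infused reflects those procedures as well as any effect of the transplant. With a single arm, no comparison group has the same preparation without FMT, so the two cannot be separated at this time point.

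The stool record has a more specific problem. Lavage is meant to produce loose stool, and PEG may reasonably be logged as a GI medication. Either is enough to make a day abnormal under the stated rule, and a higher percentage is read as worse symptoms. The protocol thus requires a procedure and then lets its outcome definition score that procedure as disease.

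The direction of bias depends on where the lavage day is recorded. Inside the treatment period it counts against FMT at that point. Inside the pre-FMT record it raises the baseline, and every later change looks better than it is.

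**Working it through.** **1. The plan's own calculation.** The only design calculation is in Section 2.8 and concerns CARS at 12 months.
- Inputs: SDs 6.5 and 6.7, r = 0.5, difference 4.2, two-sided alpha 0.05, power 80%, dropout 20%.
- σd = √(6.5² + 6.7² − 2 × 0.5 × 6.5 × 6.7) = √43.59 = 6.60.
- n = (1.96 + 0.8416)² × 6.60² / 4.2² = 19.4, rounded up to 20; 20 / 0.80 = 25; 30 are planned.

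This reproduces. CARS is not measured during FMT, so nothing below changes it.

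**2. Share of time points (Sections 2.5.1 and 2.5.2).** Post-baseline points: 1 during FMT + 6 weekly + 4 at months 3 to 12 = 11. One of 11 (9.1%) is affected; 10 remain without it.

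**3. DSR inside the treatment period.** Let k be the number of lavage days within Days 1 to 5. The document gives no value. One lavage before Day 1 gives k = 0; lavage on every infusion day gives k = 3. Let p be the share of other days that are abnormal anyway (assumed), and take each lavage day as scored abnormal.

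Recorded share = (k + (5 − k)p) / 5

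| k | Lavage days / 5 | p = 20% | p = 40% | p = 60% |
|---|---|---|---|---|
| 0 | 0% | 20% | 40% | 60% |
| 1 | 20% | 36% | 52% | 68% |
| 2 | 40% | 52% | 64% | 76% |
| 3 | 60% | 68% | 76% | 84% |

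**4. DSR if one lavage day is logged as pre-FMT.** The length of the baseline diary is not stated; 7 and 14 days are assumed. With p = 40%:
- 7 days: (1 + 6 × 0.40) / 7 = 48.6%, which is 8.6 points too high.
- 14 days: (1 + 13 × 0.40) / 14 = 44.3%, which is 4.3 points too high.

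A child with no true change would appear to improve by that amount at every later visit.

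**5. GSRS.** The protocol gives no figure for the effect of the procedures. Assume that they add s = 0.25 to 1.0 to the mean item score at the treatment-period point.
- Shift in an equally weighted average over 11 points: s / 11 = 0.02 to 0.09. This is small.
- Responder rule applied at that point, with an assumed baseline mean of 3 and a true 50% reduction: 1 − (1.5 + s) / 3 = 42% at s = 0.25 and 17% at s = 1.0. The child is a non-responder at that visit only because of the procedures.

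**The case against.** The strongest reply is that a timeframe entry is a collection schedule, not an analysis rule. Collecting GSRS and DSR during treatment has a sound purpose, since Section 2.6 uses both for safety. Which visits enter a model, and how time is coded, are commonly left to the analysis plan. That is fair, and it rules out several stronger readings that a reader might draw:

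- **That a paired test at the treatment-period visit is planned.** Section 2.7.1 speaks of comparisons with specific follow-up points and does not name them. Such a test is possible, not stated.
- **That the point would bend a linear time trend.** No time coding is given. With visit as a category, this point has its own estimate and later contrasts are essentially unaffected.
- **That at least 20% of treatment days are abnormal by definition.** A single lavage before Day 1 gives 0 of 5, and the rule does not say whether lavage counts as GI medication.
- **That fasting distorts the scores.** The fast lasts 2 hours after each infusion, which is a weak mechanism.
- **That the week 1 visit is contaminated as well.** No GSRS recall period is stated, so this cannot be judged.

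In addition, the list of clinical data that opens Section 2.7.1 omits DSR. It enters the mixed model only through the general reference to secondary outcomes.

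What remains is what the protocol itself fixes: the treatment period is named as an outcome time point, the longitudinal model covers these outcomes without setting it aside, the responder rule has no visit attached, and the abnormal-day rule has no exemption for a bowel preparation that every child receives.

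**Conclusion.** The point holds as a minor, easily corrected flaw. The stated rules allow the required lavage to be scored as worse symptoms: 0 to 3 of 5 treatment days (0% to 60%), depending on timing that the document does not give. If a lavage day falls in the pre-FMT record, the error reverses and favours FMT, by about 4 to 9 percentage points under the assumed diary lengths and an underlying share of 40%.

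That the procedures distort the scores is an inference. It is near certain for PEG and stool consistency, and plausible for GSRS through lavage, diet and tube discomfort. The sizes for GSRS rest on an assumed shift.

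A reader might infer that the trial's main results are at risk. The documents do not support that. Section 2.7.1 places the primary endpoint assessment at 12 months, and the sample size rests on 12-month CARS. The 12-month comparisons change only where the stool-record baseline includes a lavage day.

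**What to change.** Keep collecting everything as scheduled, and change only the analysis wording:

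1. In Sections 2.5.1, 2.5.2 and 2.7.1, label treatment-period GSRS and DSR as tolerability data. Leave them out of the efficacy mixed model and the GSRS responder rule.
2. In the DSR definition, state that days affected by protocol-required bowel preparation are not counted as abnormal, neither as GI medication use nor for stool consistency caused by lavage. Remove those days from both numerator and denominator of the percentage.
3. Apply the same rule to the pre-FMT record, so that a lavage day before Day 1 cannot raise the baseline.

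The cost is that one of 11 post-baseline points is no longer used for efficacy, and a baseline diary may lose a day. No visit, procedure or sample size changes.
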